### Implementation {16c}

The principal author will generate the allocation sequence for the trial within the REDCap database. A clinical research associate will enroll participants on the basis of this allocation.

## Assignment of interventions: blinding

### Who will be blinded {17a}

Trial participants and care providers will be blinded to group assignment. Trial data will be given by participants and, after data lock, data analysts will be unblinded to grouping to compare questionnaire scores between groups.

### Procedure for unblinding if needed {17b}

Not applicable: given the fictitious nature of the Dummy Trial, there is no procedure in place for unblinding of group allocation.

## Data collection and management

### Plans for assessment and collection of outcomes {18a}

The primary study instrument (Feedback Session questionnaire) is provided in Additional file 1. It is derived, for greater fidelity to the peri-operative patient population, from two validated tools for the measurement of undue influence: the Iowa Coercion Questionnaire [25] and Coercion Assessment Scale [26].

### Plans to promote participant retention and complete follow-up {18b}

Not applicable: the trial period is extremely brief, and we do not anticipate difficulty with participant retention or completion of follow-up.

### Data management {19}

All information gathered during the course of the study will anonymized and stored in a secure, locked file cabinet. Only research personnel will have access to the cabinet key. Survey data will be extracted by a study team member blinded to group allocations into a secure REDCap database managed by the trial steering committee.

### Confidentiality {27}

Patient numbers will be used instead of names to ensure confidentiality upon entry and analysis of data. When results are prepared for presentation or publication, they will be presented in a way that makes it impossible to identify individual participants.

### Plans for collection, laboratory evaluation, and storage of biological specimens for genetic or molecular analysis in this trial/future use {33}

Not applicable: biological specimens will not be collected in the described trial.

## Statistical methods

### Statistical methods for primary and secondary outcomes {20a}

We will use descriptive statistics to summarize demographic information and baseline characteristics. We will reorder item responses from least to greatest perception of coercion (e.g., “someone tried to force me to be in this study” would be unchanged, with 1 = “not at all”, while “I chose to be in this study” would flip such that 1 represents “very much so) to calculate overall undue influence scores for each discrete section and the questionnaire as a whole. We will perform chi-square tests for ordinal responses to each item on the study questionnaires. We will also define the total average score for each questionnaire as the sum of individual item answers divided by the total questions answered, resulting in a continuous measure ranging from 1 to 4. To compare these average scores in patients approached for research consent prior to or on the day of surgery, we will use t-tests or non-parametric Wilcoxon tests.

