### Outcomes {12}

The primary outcome is participants’ score on the post-operative questionnaire, which is designed to reflect perceptions of undue influence to consent to participation in the Dummy Trial.

Secondary outcomes include patients’ perceptions of how informed they were with respect to the consent provided to participate in the Dummy Trial, and rate of enrollment in the Dummy Trial. In addition, an exploratory secondary analysis is planned to examine the potential relationships between participants’ demographic variables and the primary outcome.

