### Sample size {14}

Based on our hypothesis that voluntariness will be similar between the two study groups, this trial is powered as a non-inferiority RCT. Drawing on data from previous reports validating the questionnaires adapted for this trial [26], we calculate that a sample size of 102 patients (51 in each group) will be needed to assess that the intervention group is non-inferior to the control group with 80% power (alpha = 0.05), with respect to the main outcome defined as the average questionnaire score (continuous measure ranging from 1 to 4), using a two-sample equal-variance *t*-test. We assumed a non-inferiority margin of − 0.3 and a common standard deviation of 0.6 (assumed to be a 5th of the average score range). In order to account for the assumed at most 10% of patients who would decline to participate in this Feedback Session, having not enrolled in the Dummy Trial, the randomization sample size will be 114 patients (57 in each group). The sample size was computed using PASS 2023, version 23.0.2.

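### Item responses are called ordinal but compared with chi-square tests, which, read as Pearson tests, ignore the order and cost roughly 11 to 21 points of power against a rank-sum test (minor; item-level analysis only)

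*Protocol article*

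**What the plan says.** In the Protocol article, the section on statistical methods for primary and secondary outcomes {20a} first puts the items in a common direction: "We will reorder item responses from least to greatest perception of coercion". It then fixes the item-level test: "We will perform chi-square tests for ordinal responses to each item on the study questionnaires". No trend or Mantel-Haenszel version is named, and no exact version for small cells.

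The same section averages the answered items into a score from 1 to 4 and, to compare the arms on it, says "we will use t-tests or non-parametric Wilcoxon tests". The Outcomes section {12} places the main question at that level: "The primary outcome is participants’ score on the post-operative questionnaire". The Sample size section {14} also works on the average score: "We assumed a non-inferiority margin of − 0.3 and a common standard deviation of 0.6".

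**The concern.** A Pearson chi-square on a table of two arms by four levels gives the same p-value if the four levels are shuffled. It therefore makes no use of the ordering the plan has just constructed. When one arm is shifted towards more perceived pressure, the test spreads that signal over 3 degrees of freedom instead of concentrating it on one.

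What is at stake is the sensitivity of the item-level results. One particular form of pressure could show on a single item and be diluted in an average over all of them. With about 51 patients per arm there is little power to spare.

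**Working it through.** **1. The plan's own figure.** Inputs from the Sample size section: margin 0.3 in absolute value, SD 0.6, 80% power, alpha 0.05. For a two-sample t-test the noncentrality is 0.3 / (0.6 × √(2/n)). At one-sided 0.05, power is 0.799 for n = 50 and 0.806 for n = 51, so 51 per group reproduces. Inflation: 102 / (1 − 0.10) = 113.3, rounded up to 114, which also reproduces ("the randomization sample size will be 114 patients (57 in each group"). This calculation concerns the average score only. The item check takes n = 51 per arm from it.

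**2. One case by formula.** Assume control responses of 25/25/25/25% over levels 1 to 4 and a proportional-odds shift of 2. The other arm then has 14.3/19.0/26.7/40.0%.

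- Pearson: noncentrality = n × Σ (p0 − p1)² / (p0 + p1) = 51 × (0.0292 + 0.0080 + 0.0005 + 0.0346) = 51 × 0.0724 = 3.69. With 3 df and critical value 7.81, power is 0.33.
- Linear trend: means 2.50 and 2.92, pooled variance 1.248, so z = 0.424 / √(2 × 1.248 / 51) = 1.92. Two-sided power at 0.05 is 0.48.

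**3. Simulation over a range.** 20,000 pairs of samples per scenario, 51 against 51, two-sided 0.05. Tests: Pearson (df = occupied levels − 1), tie-corrected Wilcoxon and 1-df linear trend. The category percentages and odds ratios (OR) are assumptions, because the protocol gives none.

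| Control, levels 1–4 (%) | OR 2: Pearson / Wilcoxon / trend | OR 3: Pearson / Wilcoxon / trend | Pearson size | Expected count per arm, no difference |
|---|---|---|---|---|
| 25/25/25/25 | 0.338 / 0.488 / 0.489 | 0.712 / 0.856 / 0.852 | 0.050 | 12.8 in each |
| 50/25/15/10 | 0.323 / 0.474 / 0.465 | 0.710 / 0.853 / 0.849 | 0.047 | 25.5, 12.8, 7.6, 5.1 |
| 70/15/10/5 | 0.259 / 0.403 / 0.382 | 0.647 / 0.806 / 0.787 | 0.043 | 35.7, 7.7, 5.1, 2.6 |
| 80/12/5/3 | 0.205 / 0.337 / 0.307 | 0.547 / 0.729 / 0.681 | 0.035 | 40.8, 6.1, 2.6, 1.5 |
| 90/6/3/1 | 0.110 / 0.218 / 0.196 | 0.324 / 0.530 / 0.476 | 0.023 | 45.9, 3.1, 1.5, 0.5 |

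The first row at OR 2 agrees with step 2.

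- Loss against Wilcoxon: from 0.218 − 0.110 = 0.108 to 0.530 − 0.324 = 0.206, or about 11 to 21 points.
- Loss against linear trend: from 0.196 − 0.110 = 0.086 to 0.476 − 0.324 = 0.152, or about 9 to 15 points.
- Type I error: Wilcoxon stays at 0.048 to 0.051. Pearson falls as the floor grows and never exceeds 0.050.
- Small cells: no expected count is below 5 up to a 50% floor; the top level drops to 2.6 at 70% and 0.5 at 90%.

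**The case against.** **The wording may already mean a trend test.** A chi-square test for ordinal responses could be a chi-square for trend, which uses the order. That is possible, but the unqualified term ordinarily means Pearson. Two analysts could run tests whose power differs by 9 to 15 points here, so the test should be named in either case.

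**Pearson has a legitimate use.** It can detect non-monotone differences, which the proportional-odds simulations exclude by construction. This stands. The quoted loss applies to a consistent shift, the pattern that reordering by coercion points to.

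**Sparse cells might be taken as certain.** The documents do not support that. The section on the current state of knowledge reports that same-day patients mostly see participation as voluntary, so clustering at level 1 is plausible, but no distribution on this scale is given. A severe floor on every item also sits badly with the planning SD of 0.6. An item at 90/6/3/1 has SD 0.50, and an average over items cannot have a larger SD than the mean item SD. The 0.6 is itself an assumption and single items may differ, so this limits the scenario without ruling it out.

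**A reader might infer that the test becomes invalid.** It does not in these scenarios. The approximation is poor when cells are small, but the error is towards conservatism.

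**A reader might infer that insensitive item tests tilt the trial towards its hypothesis of similarity.** The protocol attaches no margin, power claim or decision rule to the items, and nowhere says that a non-significant item will count as evidence of similarity.

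**Conclusion.** The point holds as a minor one. The plan orders the responses, calls them ordinal, and then states a test that on its usual reading ignores the order. At 51 per arm this costs about 11 to 21 percentage points of power against Wilcoxon and about 9 to 15 against a linear trend test. The loss is present with evenly spread responses, so it does not depend on a floor effect.

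These sizes rest on assumed category distributions, a proportional-odds shift of 2 to 3, and the Pearson reading. Conservatism (size down to 0.023) arises only if responses cluster heavily at level 1. The primary comparison of average scores and the sample size of 102, inflated to 114, are unaffected.

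**What to change.** In the section on statistical methods {20a}, replace the item-level chi-square with one named order-respecting test: a tie-corrected or exact Wilcoxon rank-sum test, a linear trend test, or a proportional-odds model by arm. Wilcoxon fits most easily, because the section already names it for the average scores. If a trend chi-square was intended, say so.

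For each item, report an effect estimate (odds ratio, or the probability that a patient in one arm scores higher than a patient in the other) with its confidence interval, and label these results descriptive.

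The cost is a change of wording. The data, the sample size and the primary analysis stay as they are, and standard software covers every option.

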## Objectives {7}

We aim to determine whether a patient’s consent to participate in a low-risk clinical anesthesia research trial obtained on the same day as their surgery is as voluntary as consent obtained prior to the day of surgery. The voluntariness of consent will be determined based on the patient’s perceptions of undue influence using an adaptation of the Iowa Coercion Questionnaire [25] and Coercion Assessment Scale [26].

We hypothesize that patients from whom consent for trial participation is obtained on the same day as surgery will report similar voluntariness, as measured by perceptions of undue influence, as those in whom consent for participation was obtained prior to the day of surgery.

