## Trial design {8}

Due to the present study’s focus on measuring undue influence, which may not be consciously perceived by patients and is uniquely vulnerable to bias, the described trial relies on an element of deception (similar to psychological studies of phenomena in which nondeceptive procedures are not feasible) [27]. We propose a prospective single-blinded randomized controlled non-inferiority trial (the ‘Consent Study’) examining the voluntariness of patient consent to participate in an anesthesia research trial (the ‘Dummy Trial’; a fictitious low-risk randomized clinical anesthesia research trial) at Women’s College Hospital (WCH) when such consent is obtained (a) prior to the day of surgery compared to (b) on the same day as surgery compared to. The study design is illustrated as a flow diagram (provided in Fig. 1), and presented here in the form of a SPIRIT Figure.

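### The trial is designed and powered for non-inferiority with a margin of 0.3, but the stated analysis of the main outcome makes no reference to the margin and, taken as a test of difference, cannot establish non-inferiority

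*Protocol article*

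**What the plan says.** Trial design {8} describes a "prospective single-blinded randomized controlled non-inferiority trial". Objectives {7} hypothesizes that patients who consent on the day of surgery "will report similar voluntariness, as measured by perceptions of undue influence", compared with those who consent earlier.

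Sample size {14} states that "this trial is powered as a non-inferiority RCT". It takes the average questionnaire score as the main outcome and names an equal-variance two-sample t-test. It sets the number needed to assess that the same-day group is "non-inferior to the control group with 80% power (alpha = 0.05"). It continues: "We assumed a non-inferiority margin of − 0.3", with "a common standard deviation of 0.6 (assumed to be a 5th of the average score range"). The result is 51 evaluable patients per group, raised to 57 per group for non-participation of up to 10%.

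Statistical methods {20a} recodes the items so that a higher score means more perceived coercion, and defines the average score. It then says that, to compare these scores between the two timings of consent, "we will use t-tests or non-parametric Wilcoxon tests". It gives no margin, shifted null hypothesis, confidence limit or sidedness. Sections {20b} and {20c} add none. The margin appears only in {14}.

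**The concern.** A t-test or Wilcoxon test used simply to compare two groups has equality as its null hypothesis. Failing to reject equality does not show that the excess in perceived coercion is smaller than 0.3. That conclusion needs the difference to be tested against the margin, or a confidence limit to be set beside it. Section {20a} names the test for the main outcome but leaves out the one element that makes it a non-inferiority test.

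The Wilcoxon alternative makes this harder to resolve. The margin is 0.3 points on the mean score, and a rank test does not estimate or test a difference in means, so nothing in the text connects it to the margin.

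The risk is lopsided. The investigators expect similarity. If similarity were inferred from a non-significant comparison, small or incomplete data would make that conclusion more likely. The results are meant to inform guidance on how much time patients should have before consenting, so false reassurance would matter.

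**Working it through.** **Inputs.** From {14}: margin 0.3 in size, SD 0.6 (one fifth of the score range, (4 − 1)/5), 51 per group, alpha 0.05, power 80%, equal-variance t-test. Assumed, because not stated: a true difference of 0 for the power calculation, and one-sided alpha. Both are checked by whether they return the stated number. Differences below are same-day minus clinic (PAC), so positive means more perceived coercion on the day of surgery.

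**Step 1: reproduce the plan's number.**
- SE = 0.6 × √(2/51) = 0.1188, with 100 degrees of freedom.
- Non-inferiority t-test, one-sided 0.05: noncentrality 0.3/0.1188 = 2.53 and critical value 1.660. Power is 80.6%, and 51 per group is the smallest size that reaches 80%. This is an exact match.
- Inflation: 102/0.9 = 113.3, so 114 (57 per group), as stated.
- Alternatives: one-sided 0.025 needs 128 in total (exact t). A two-sided 0.05 test to detect a difference of 0.3 needs about 126. Neither gives 102.

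The number in {14} is therefore that of a one-sided 0.05 t-test against the margin.

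**Step 2: compare the two decision rules at 51 per group and SD 0.6.**
- Test of difference, two-sided 0.05: non-significant if the observed difference is smaller in size than 1.984 × 0.1188 = 0.236.
- Non-inferiority, one-sided 0.05: concluded if the observed difference is below 0.3 − 1.660 × 0.1188 = 0.3 − 0.197 = 0.103.

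Observed differences between about 0.10 and 0.24 are non-significant yet fail non-inferiority. For example, at an observed 0.235 the upper 90% limit is 0.235 + 0.197 = 0.43, well beyond the margin.

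**Step 3: how often each rule would give a favourable result** (noncentral t). The middle column counts non-significance as favourable, which is a hypothetical reading.

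| True excess | Non-significant, two-sided 0.05 | Non-inferiority concluded, one-sided 0.05 |
|---|---|---|
| 0 | 95.0% | 80.6% |
| 0.1 | 86.7% | 51.1% |
| 0.2 | 61.5% | 20.9% |
| 0.3 | 29.4% | 5.0% |

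**Step 4: dependence on sample size.** At a true excess of 0.3, non-significance occurs in 24.6% of trials with 57 per group, 52% with 30 and 66% with 20. The non-inferiority test holds this error at 5% whatever the size.

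**The case against.** The strongest reply is that {14} already supplies most of the specification: outcome, t-test, margin and alpha. The number reproduces exactly as a margin-shifted t-test, and {20a} names the same outcome and the same family of test. Read together, the t-test in {20a} may have been meant as the non-inferiority test. That is a fair reading, and it makes the defect one of wording that can be repaired. It does not remove the defect, because {20a} does not say so and offers a Wilcoxon alternative that the reading cannot cover.

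A second reply is that confidence limits and decision rules are commonly left to an analysis plan or full protocol. Their absence alone would be no finding. Here, however, the article does name the test, and the test as worded does not match the design.

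Two stronger readings are not supported:
- A reader might infer that the investigators will treat a non-significant p-value as evidence of similarity. No section says this. The error rates for the test of difference apply only if that were done.
- A reader might infer that the ordinary test could also condemn a trivial difference well inside the margin. At SD 0.6 it cannot: a harmful difference is significant only above 0.236, and non-inferiority has already failed above 0.103. For the two rules to conflict that way, the SD must be below 0.6 × 0.3/(0.236 + 0.197), or about 0.42, which the protocol does not assume.

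**Conclusion.** The point holds as a mismatch between design and stated analysis. The trial is sized for a one-sided non-inferiority t-test, while {20a} describes a comparison that omits the margin and, followed as an ordinary test of difference, cannot answer the objective.

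The potential size is a 29% chance of a favourable conclusion at a true excess equal to the margin, against 5% for the non-inferiority test, and 62% against 21% at an excess of 0.2. These figures assume 51 per group, SD 0.6 and normal-theory t-tests, and they are conditional on non-significance being read as similarity. The sample size calculation itself is sound on its stated inputs, once alpha is taken as one-sided.

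**What to change.** In {20a}, state that:
- the primary analysis is the same-day minus clinic difference in mean average score, with a two-sided 90% confidence interval;
- non-inferiority is concluded if the upper limit is below +0.3;
- the Wilcoxon test is supportive only;
- a non-significant test of difference will not be interpreted as similarity.

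This changes or settles three things, which should be acknowledged openly:
- **Sidedness.** Section {14} does not say whether alpha is one- or two-sided. Label it one-sided 0.05, the only reading found to reproduce 102.
- **Sign.** Section {14} writes the margin as −0.3, but after the recoding in {20a} the harmful direction is positive. State the direction of the difference and reconcile the sign.
- **Wilcoxon.** It moves from an alternative primary test to a supportive one.

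The cost is wording only, submitted as an amendment under {25} and settled before outcome data are seen. Sample size and conduct are unchanged if one-sided 0.05 is kept. If a two-sided 95% interval were preferred, power at 51 per group falls to 70.6%. Reaching 80% would then take 64 evaluable per group (128 in total), or 64/0.9 = 71.1, so 72 randomized per group (144 in total).

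### The primary comparison may be made by t-test or Wilcoxon, but the 0.3 margin and the sample size belong to a difference in means, which a Wilcoxon test does not in general address

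*Protocol article*

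**What the plan says.** In the Protocol article, Sample size {14} states that "this trial is powered as a non-inferiority RCT". The main outcome there is the average questionnaire score on a 1 to 4 scale, and the 51 patients per group are derived "using a two-sample equal-variance *t*-test". On the margin and spread it says: "We assumed a non-inferiority margin of − 0.3 and a common standard deviation of 0.6".

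Statistical methods for primary and secondary outcomes {20a} sets the direction of the score: "We will reorder item responses from least to greatest perception of coercion". After recoding, 1 is therefore the most favourable value and also the lowest possible one. The section then says that average scores in the two groups will be compared by "t-tests or non-parametric Wilcoxon tests". It gives no rule for choosing between the two tests, does not mention the margin, and does not say how a rank-test result would be judged against 0.3. No other section of the article settles this.

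**The concern.** The two tests answer different questions. The t-test concerns the difference in means, which is what the margin and the sample size are written in. The Wilcoxon test concerns rank order: whether a same-day patient tends to score above an advance-consent patient.

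If same-day consent did harm, one plausible pattern is a minority who felt strongly pressured. Their scores move the mean by the full amount, whereas the rank test registers little beyond the fact that they are high. The trial is meant to inform consent guidelines, so a non-inferiority claim resting on a test that does not address the stated margin could mislead in the direction that matters.

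**Working it through.** **1. Which hypothesis the sample size belongs to.** Inputs from {14}: margin 0.3, SD 0.6, power 80%, alpha 0.05. Sidedness is not stated. The true difference is taken as 0, from the hypothesis that the groups are similar.

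- Normal approximation, one-sided 0.05: n = 2 × 0.6² × (1.645 + 0.842)² / 0.3² = 49.5, so 50 per group.
- Exact noncentral t: noncentrality = 0.3 / (0.6 × √(2/51)) = 2.52 on 100 df. Power is 80.6% at 51 per group, the smallest n that reaches 80%.
- One-sided 0.025 would need 64 per group; 51 would give 70.6%.
- Allowing for 10% loss: 102 / 0.9 = 113.3, so 114.

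The plan's 51 and 114 reproduce, as a one-sided 5% test of a **difference in means**.

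**2. What a Wilcoxon test would be testing.** The ordinary version tests equality, and 0.3 appears nowhere in it. To bring in the margin, one could subtract 0.3 from each same-day score and test whether the shifted scores rank below the controls. That is valid for the mean margin if the two distributions differ only by a shift. A score bounded at 1 with patients on the bound cannot shift this way. After subtraction, a same-day patient at 1.0 becomes 0.7 and ranks below every control. If a share f of the same-day group is at the floor, then

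P(shifted same-day score < control score) ≥ f,

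while the null value of the rank test is 0.5. At f = 0.60 this probability is at least 0.60 however high the remaining 40% score.

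**3. Size at the boundary.** The floor share and score shape are assumptions. The true mean difference is 0.3 (within 0.003 in the item-level models), with 51 per group and one-sided 5%. The two-part models use mean = 1 + (1 − floor share) × (off-floor mean − 1). For example, off-floor uniform on 1.1–3.1 has mean 2.1. A 70% floor gives 1 + 0.30 × 1.1 = 1.33 for advance consent, and a 43% floor gives 1 + 0.57 × 1.1 = 1.63 for same-day.

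| Score model | Floor share, advance / same-day (%) | t bound declares NI (%) | Shifted Wilcoxon declares NI (%) | Ordinary Wilcoxon p > 0.05 (%) |
|---|---|---|---|---|
| Normal, SD 0.6 | none assumed | 4.9 | 4.9 | 31.8 |
| Uniform 1.1–2.5 | 50 / 12.5 | 4.1 | 3.3 | 7.3 |
| Uniform 1.1–2.5 | 70 / 32 | 4.8 | 16.9 | 5.1 |
| Uniform 1.1–3.1 | 50 / 23 | 4.8 | 8.8 | 31.7 |
| Uniform 1.1–3.1 | 60 / 33 | 4.4 | 18.1 | 28.5 |
| Uniform 1.1–3.1 | 70 / 43 | 4.9 | 39.4 | 24.2 |
| Uniform 1.1–3.1 | 80 / 53 | 5.0 | 71.2 | 17.6 |
| Uniform 1.1–3.1 | 90 / 63 | 5.1 | 94.0 | 8.0 |
| Uniform 1.5–4 | 80 / 63 | 5.2 | 91.2 | 53.6 |
| Ten items, 1–4 | 4 / 1 | 4.9 | 4.2 | 26.4 |
| Ten items, 1–4 | 24 / 11 | 5.0 | 10.7 | 25.1 |
| Ten items, 1–4 | 41 / 21 | 5.4 | 28.8 | 19.3 |
| Ten items, 1–4 | 53 / 29 | 6.1 | 50.6 | 15.0 |
| Beta tail, excess all in tail | 30 / 30 | 5.8 | 37 | 57 |
| Beta tail, excess all in tail | 50 / 50 | 5.8 | 74 | 77 |
| Beta tail, excess all in tail | 60 / 60 | 6.8 | 90 | 85 |

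There were 20,000 runs for the normal row, 4,000 for the beta rows and 6,000 for the others. In the 70 / 43 row the advance-consent SD is 0.60, the protocol's own value.

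Tail shape matters as much as floor share. With equal floors of 30, 50 and 60%, another beta tail gave 15, 56 and 84%, and floors of 10% or less gave about 5%. When the difference arose from floor share instead, beta-tail models gave 3% (30 / 0), 4% (40 / 10), 8.5% (50 / 20) and 17% (60 / 30).

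**The case against.** **Choice of test is ordinary SAP content.** The article condenses a fuller protocol that is not shown, and {14} already names the t-test. This would dispose of the point if the article were merely silent. Instead it states an alternative in its analysis section, and that alternative does not test the hypothesis the trial is powered for. A later plan that settled on one test would have to override {20a}, not fill a gap in it.

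**The shifted Wilcoxon is not in the protocol.** This is correct. Its error rates show what happens under one natural way of applying the margin, not under a stated plan. Likewise, the last column is an error rate only if a non-significant result is read as similarity, which the article does not say.

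**The large figures rest on chosen distributions.** This also stands. A reader might take 37–90% as the false non-inferiority rate, but that range belongs to models with the same floor share in both groups and the whole excess in the upper tail. Other reasonable models give 3–18%.

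**Floor-heavy scores are assumed.** A reader might infer that the Wilcoxon branch is the likely one. The Background reports little perceived coercion in earlier work, so low scores are plausible. However, an average of exactly 1 needs the most favourable answer on every item answered, reversed items included. The documents do not show how common that will be.

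**Selection after unblinding.** A reader might infer that analysts would pick the test once they know the groups, because Who will be blinded {17a} says that after data lock "data analysts will be unblinded to grouping to compare questionnaire scores between groups". That sentence dates the unblinding, not the choice of test. No such claim is made here.

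**Conclusion.** The point holds as an inconsistency between two sections. The margin and sample size in {14} are for a difference in means, and {20a} permits a test that either ignores the margin or addresses it only under a pure location shift.

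The consequence runs from none to severe. At a true difference equal to the margin, a shifted Wilcoxon would declare non-inferiority in about 3% to over 90% of trials, depending on the floor share, on whether it differs between groups, and on the shape of the upper tail. A t-based bound stays at about 4–7% in every model tried, including floor-heavy ones. No single figure can be given, because the article reports no score distribution.

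The planned sample size is not in dispute. Nor is the equal-variance t-test shown to be inadequate: where the equal-variance and Welch versions were run side by side, their error rates were practically identical.

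**What to change.** In {20a}, name one primary analysis: the difference in mean average score, same-day minus advance, with a t-based one-sided 95% upper confidence limit. Declare non-inferiority if the limit lies below +0.3. The positive sign follows from the recoding in {20a}, where higher means more perceived coercion; {14} writes the margin as −0.3, so the two should be aligned. The planned equal-variance t is acceptable, and Welch is optional.

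Add a bootstrap interval for the same mean difference as the check on skewness, and keep the Wilcoxon test as descriptive only. State this before any grouped data are examined.

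The cost is a change of wording. The 51 per group (114 randomised) and the 80.6% power at one-sided 0.05 are unaffected.
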